## Abstract

**Background:**

High flow nasal cannula (HFNC) has been increasingly adopted in the past 2 decades as a mode of respiratory support for children hospitalized with bronchiolitis. The growing use of HFNC despite a paucity of high-quality data regarding the therapy’s efficacy has led to concerns about overutilization. We developed an electronic health record (EHR) embedded, quality improvement (QI) oriented clinical trial to determine whether standardized management of HFNC weaning guided by clinical decision support (CDS) results in a reduction in the duration of HFNC compared to usual care for children with bronchiolitis.

**Methods:**

The design and summary of the statistical analysis plan for the REspiratory SupporT for Efficient and cost-Effective Care (REST EEC; “rest easy”) trial are presented. The investigators hypothesize that CDS-coupled, standardized HFNC weaning will reduce the duration of HFNC, the trial’s primary endpoint, for children with bronchiolitis compared to usual care. Data supporting trial design and eventual analyses are collected from the EHR and other real world data sources using existing informatics infrastructure and QI data sources. The trial workflow, including randomization and deployment of the intervention, is embedded within the EHR of a large children’s hospital using existing vendor features. Trial simulations indicate that by assuming a true hazard ratio effect size of 1.27, equivalent to a 6-h reduction in the median duration of HFNC, and enrolling a maximum of 350 children, there will be a > 0.75 probability of declaring superiority (interim analysis posterior probability of intervention effect > 0.99 or final analysis posterior probability of intervention effect > 0.9) and a > 0.85 probability of declaring superiority or the CDS intervention showing promise (final analysis posterior probability of intervention effect > 0.8). Iterative plan-do-study-act cycles are used to monitor the trial and provide targeted education to the workforce.

**Discussion:**

Through incorporation of the trial into usual care workflows, relying on QI tools and resources to support trial conduct, and relying on Bayesian inference to determine whether the intervention is superior to usual care, REST EEC is a learning health system intervention that blends health system operations with active evidence generation to optimize the use of HFNC and associated patient outcomes.

**Trial registration:**

ClinicalTrials.gov NCT05909566. Registered on June 18, 2023.

**Supplementary Information:**

The online version contains supplementary material available at 10.1186/s13063-024-08327-y.

## Background

Bronchiolitis is the most common reason for admission to the hospital in the first year of life and high flow nasal cannula (HFNC) is an increasingly common mode of respiratory support for hospitalized children with bronchiolitis [1]. Between 2012 and 2019, the rate of initiation of HFNC for children presenting to a large children’s hospital emergency department with bronchiolitis significantly increased from 1.3 to 17.0%, without any associated change in the rates of hospital or intensive care unit admission [2]. Between 2010 and 2019, the use of HFNC among children admitted to intensive care at another large children’s hospital significantly increased, while over the same period there was a sevenfold increase in encounters receiving an administrative code for noninvasive ventilation, likely explained by an increase in the use of HFNC [3].

Despite this uptrend in use, data regarding the impact of HFNC on outcomes of children with bronchiolitis are mixed [4]. Randomized, controlled trials have both demonstrated HFNC as reducing the need for escalation of care [5, 6], as well as having no effect on the need for escalation in care [7]. The collective findings of observational studies have been similarly inconclusive, with the use of HFNC associated with decreased [8–11], increased [12], or no difference [13, 14] in the need for intensive care admission or invasive mechanical ventilation. The rise in the use of HFNC for bronchiolitis in the absence of high-quality data regarding efficacy has led to scrutiny regarding the financial costs and personnel time associated with HFNC, while raising the question “is HFNC being overutilized?” [15, 16]. The American Academy of Pediatrics guidelines for the management of bronchiolitis were last updated in 2014 and do not advise on the use of noninvasive respiratory support, underscoring uncertainty regarding how to use HFNC in the management of children with bronchiolitis [17]. In an effort to curb excess HFNC utilization, many children’s hospitals have implemented standard management guidelines, which are increasingly coupled with electronic health record (EHR) workflows, for the use of HFNC for children with bronchiolitis. However, without established best practices for the use of HFNC, it is unclear whether such standardized guidance and related clinical decision support (CDS) meaningfully affect patient outcomes. Moreover, imposing unproven CDS on strained staff risks potentiating burnout in the absence of any benefit to patient care [18].

During the 2022–2023 pediatric respiratory virus surge (“tripledemic”), our own institution experienced an exceptionally high volume of children with respiratory viruses, prompting the development of a local clinical effectiveness guideline outlining a standardized approach to weaning HFNC following its initiation for hospitalized children with bronchiolitis. To promote adherence to the standardized weaning pathway, CDS was designed requiring regular assessments by bedside nurses or respiratory therapists. To ensure that the CDS and related standard weaning pathway is a value-added contribution of patient care, our team designed a randomized, EHR-embedded, pragmatic, Bayesian clinical trial leveraging the support of local quality improvement (QI) teams and processes. We describe the overarching trial design, the embedded electronic workflow, the EHR data informatics pipeline constructed to support trial analyses, the results of trial simulations to inform the trial design, and the statistical analysis plan for the ongoing REspiratory SupporT for Efficient and cost-Effective Care (REST EEC; “rest easy”) trial.

### Aim

The objectives of the REST EEC trial are to (1) determine whether a CDS intervention coupled with a clinical effectiveness guideline is effective at reducing the duration of HFNC for bronchiolitis compared with usual care at a large children’s hospital; (2) demonstrate the utility of embedded randomization and associated EHR data analysis for determining whether CDS is a value-added contribution to patient care; and (3) introduce the concept of “statistically promising,” or a posterior probability of ≥ 0.8, as a meaningful Bayesian statistical conclusion for minimal-risk, QI oriented study questions.

### Study design and setting

REST EEC is a randomized, EHR-embedded, pragmatic, single-center, learning health system trial incorporating QI methodologies. The trial is being conducted at UPMC Children’s Hospital of Pittsburgh (CHP) in the United Sates and is enrolling hospitalized children with bronchiolitis who require HFNC support during admission. CHP is an approximately 300-bed standalone children’s hospital with approximately 25,000 annual inpatient and observation admissions, including between 2000 and 3000 annual admissions to the pediatric intensive care unit (PICU). The PICU has 36 dedicated beds but routinely exceeds capacity during the winter and respiratory virus season months, reaching daily censuses as high as 60 during peak patient volumes. CHP policies require children receiving HFNC to be cared for in an intensive care unit and all children with bronchiolitis who are greater than 1 month old, newly admitted to the hospital (not already admitted to the neonatal or cardiac intensive care units) and without unrepaired, cyanotic heart disease are cared for by the PICU service.

CHP uses the Cerner Millennium EHR (Oracle Cerner Corporation, Kansas City, MO). A CHP enterprise data warehouse (EDW) relies on an Oracle Data Warehouse solution (Oracle Corporation, Austin, TX), Informatica ETL (extract, transform, and load) software (Redwood City, CA) for movement and transformation of data from local EHR data sources, and Qlik software (Qlik, King of Prussia, PA) for up-to-date data visualization to support QI initiatives. This description of a clinical trial was developed to follow the SPIRIT reporting guidelines (Supplemental Checklist).

### Data collection processes

The design and statistical analysis plan for REST EEC were informed by observational data from the EHR. To inform the Bayesian adaptive design, trial simulations were performed based on current data on bronchiolitis admissions from recent years at CHP. An Informatica ETL pipeline was developed to harvest the initial data to support simulations, with the intent of then leveraging the same pipeline to both monitor trial progress and support ensuing analyses. The CHP EDW has a low latency refresh, harboring data that are commonly only seconds behind the production EHR used by clinicians for patient care. To facilitate data retrieval, a subset of the warehouse contains a “staged” rolling 3–4 years of curated, transformed, and cleansed EHR data that are highly indexed to optimize query times. The Informatica pipeline queries this staged environment and produces a single table output that contains salient patient demographics, covariates of interest, and outcomes data. Queries can be run ad hoc, and the pipeline is also being attached to a Qlik dashboard interface that refreshes nightly and will provide data on enrollment, including total enrolled and summary statistics of treatment assignments. The curated REST EEC data table can be linked with an existing intensive care EDW data mart that automatically refreshes nightly and contains salient critical care data elements such as duration of mechanical ventilation, as well as pediatric risk of mortality IV score, and pediatric logistic organ dysfunction 2 scores, as previously described, to support interim and final trial analyses [19]. As data to support trial analyses are harvested from clinical documentation, data quality is reliant on best patient care practices and periodic external audits from accrediting bodies such as the Joint Commission. Missing data will be reported as such and outliers will be adjudicated by a nurse informaticist member of the study team.

Trial conduct, interim analyses, and final analyses are also relying on observational data sources, including both the EHR and local data submitted to the Pediatric Health Information Systems (PHIS) database, which is a large, multicenter, benchmarking database for children’s hospitals that harbors predominantly administrative data including encounter dates, care-related charges, and diagnosis codes. PHIS offers additional data elements not readily retrievable from the EDW, including geographically adjusted costs of care, complex chronic comorbidities flags as defined by Feudtner et al. [20], and an additional set of risk scores providing predicted mortality (based on administrative admission data) and expected mortality (based on administrative data from the entire encounter) for use as additional balance measures. PHIS is maintained by Children’s Hospital Association (Lenexa, KS) and can be accessed using a web application version of SAP Business Objects (SAP, Walldorf, Germany). PHIS data are deidentified but can be linked to local, single center patient data via a decryption key possessed by designated individuals at the site, as we have previously done for observational studies. A data monitoring committee was not deemed necessary as the intervention is minimal risk.

### Guideline eligibility criteria and patient inclusion plan

Clinicians are guided to include patients in the REST EEC trial if the following criteria are met (Fig. 1): (1) a diagnosis of bronchiolitis per the clinical team; (2) less than 2 years of age; (3) a work of breathing (WOB) score > 2 (score calculation displayed in Fig. 1). Because a dysfunctional immune response can result in an atypical and erratic disease course, and because both chronic lung disease and certain congenital heart diseases can sufficiently alter baseline work of breathing in a way not accommodated by the WOB score, guidance is provided to clinicians to exclude patients from the REST EEC trial if any of the following criteria are present: (1) immunocompromised or immunosuppressed status; (2) presence of chronic lung disease; (3) presence of congenital heart disease with cardiorespiratory manifestations. As the REST EEC trial relies on clinicians for assessment of these eligibility criteria, patients will ultimately be included in the primary analysis if clinicians place the orders required for randomization and study entry, the patient age is < 2 years, and the patient encounter is associated with a primary or secondary diagnosis code compatible with a viral lower respiratory tract infection.

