### Randomization

The intervention is the provision of clinical decision support to guide bedside nurses and respiratory therapists in the systematic weaning of HFNC for children with bronchiolitis. The control is usual care, which consists of a clinical pathway for HFNC weaning without associated clinical decision support. Ordering clinicians are the target of randomization, but the unit of randomization is a clinician-patient decision moment. Accordingly, each time a clinician has decided to initiate HFNC for a patient eligible for REST EEC, randomization will occur in an unblinded, automated, and 1:1 ratio between the intervention and usual care arms. Only the CDS intervention is randomized and all other components of care are not specified by the study design, instead proceeding according to usual care. As the intervention involves CDS to reinforce an existing standard of care and the endpoint is duration of HFNC, a respiratory support modality that is the focus of de-implementation campaigns and not considered an established standard of care, the University of Pittsburgh Institutional Review Board approved waiver of consent for the REST EEC trial. Randomization is automated and cued by placement of a “HFNC for Bronchiolitis” Cerner PowerPlan (orderset) and based on whether a specific digit in the encounter identifier, which is a Cerner Millennium database key not readily apparent to clinicians and specific to a patient hospital encounter, is even or odd. Encounter identifiers are assigned sequentially as patients are registered for an interaction with the healthcare system, ensuring that the assignments are equally and randomly distributed between the 2 trial arms.

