To accommodate the unique patient population of interest, the clinical effectiveness guideline workflow, and the need for randomization, a “HFNC for Bronchiolitis” PowerPlan was constructed leveraging features of Cerner’s PowerFlex PowerPlan technology. PowerFlex PowerPlans allow for dynamic PowerPlan characteristics according to programmed rules that can draw upon individual patient characteristics. To ensure that patients > 2 years of age are not randomized, the “HFNC for Bronchiolitis” PowerFlex PowerPlan cannot be ordered for patients 2 years or older. If attempting to place the PowerPlan, clinicians receive a message stating that the patient is not eligible for the order and asking them to remove the PowerPlan. For patients < 2 years old, the REST EEC trial eligibility criteria are displayed at the top of the PowerPlan and clinicians are instructed to sign the PowerPlan only if patients meet the criteria (Fig. 2). The REST EEC study arms, one for the intervention and one for usual care, are both available as options within the PowerPlan, alongside instructions to clinicians stating “The pre-selected orders below are based on randomization and should only be changed if the physician/APP thinks it is in the best interest of the patient.” The randomized assignment is pre-selected using the PowerFlex feature when the PowerPlan is opened but can be changed if a clinician has a strong preference. The intervention group are those patients for whom CDS is ordered and the control group are those patients who receive usual care without CDS. A new WOB score documentation field was also built in a segment of the electronic flowsheet that overlaps with nursing and respiratory therapist workflows, allowing both disciplines to document the score as requested by the HFNC weaning guideline. REST EEC is deployed as part of usual care and all ancillary and post-trial care occur according to usual care.

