**Fig. 2 Fig2:**
[figure not shown]
Screenshot of the Cerner “Bronchiolitis HFNC Oxygen Therapy PowerPlan.” Eligibility criteria are listed at the top of the PowerPlan, with instructions to clinicians to remove the PowerPlan if the patient does not meet criteria. The green box outlines the section of the PowerPlan that is pre-selected according to the patient’s randomized assignment

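### The arm is on screen before the signature that admits a child to the primary analysis, so analysis by assignment does not guard against arm-dependent non-signing

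*Protocol article*

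**What the plan says.** **Entry to the primary analysis.** Under Guideline eligibility criteria and patient inclusion plan, "patients will ultimately be included in the primary analysis if clinicians place the orders required for randomization and study entry", the child is under 2 years, and "the patient encounter is associated with a primary or secondary diagnosis code compatible with a viral lower respiratory tract infection".

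**When the arm is seen.** Under Study intervention and associated workflow, "The randomized assignment is pre-selected using the PowerFlex feature when the PowerPlan is opened but can be changed" by the clinician. Both arms are listed as options in the plan.

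**Who judges eligibility.** In the same section, "clinicians are instructed to sign the PowerPlan only if patients meet the criteria". The Fig. 2 legend mentions "instructions to clinicians to remove the PowerPlan if the patient does not meet criteria". Apart from age, which the software enforces, the criteria (bronchiolitis, work of breathing score, immune, lung and heart exclusions) rest on the clinician's assessment.

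**Allocation.** The Randomization section calls allocation unblinded and 1:1, and bases it on whether one unnamed digit of the encounter identifier is even or odd. It states: "Encounter identifiers are assigned sequentially as patients are registered for an interaction with the healthcare system, ensuring that the assignments are equally and randomly distributed". It also states that "the unit of randomization is a clinician-patient decision moment".

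**Analysis.** The statistical section calls the primary analysis intention to treat, by randomized assignment. A modified version reflects arms changed by the ordering clinician.

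**The concern.** Intention to treat protects a comparison when everyone allocated is analysed. Here the arm appears first, and the act that creates the analysis record comes second. If the displayed arm influences whether a clinician signs, the child is lost from the analysis altogether and is not merely moved between arms. Analysing signed children by assignment cannot recover that loss.

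If clinicians signed less readily for children expected to wean slowly when CDS was displayed, the CDS arm would retain the faster weaners and look better with no true effect. The opposite pattern would hide a real effect. The decision thresholds are lenient (posterior probability above 0.9 for superiority at the final analysis, above 0.8 for promising), so a small bias moves the error rates noticeably. A promising result is enough to leave CDS in place after the trial.

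Two statements in the Randomization section also do not fit the mechanism it describes: the argument from sequential numbering, and the unit of randomization.

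**Working it through.** **1. Order of events.** HFNC is decided on; the plan is opened and the arm is shown; the clinician judges eligibility; the clinician signs or removes the plan; a signed child can enter the analysis. The arm precedes the inclusion decision. Nothing in the article brings opened-but-unsigned encounters into the primary analysis.

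**2. The plan's own figures.** Inputs from the statistical section: HR 1.27, maximum N 350, looks at 12, 18 and 24 months, 100-150 patients per year, interim superiority if P(HR > 1) > 0.99, interim futility if P(HR < 1.15) > 0.8, final thresholds 0.9 and 0.8, prior N(0, 2.5) with 2.5 read as the SD. Approximation: every child is an event and the information is events/4.

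- SE of log HR at 350 = 2/√350 = 0.107. The prior precision, 1/2.5² = 0.16, is negligible against 350/4 = 87.5.
- Final look alone: ln 1.27/0.107 = 0.239/0.107 = 2.236. Superiority: Φ(2.236 − 1.282) = 0.83. Promising or better: Φ(2.236 − 0.842) = 0.92.
- With the interim rules, by simulation at 100 / 125 / 150 patients per year: superiority 0.77 / 0.79 / 0.80, promising or better 0.83 / 0.85 / 0.865. The article gives > 0.75 and > 0.85. The first is reproduced; the second is reproduced at 150 per year and within about 2 points below that.
- At HR 1.00: superiority about 0.09, promising or better about 0.16.

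The design figures are not at fault. They assume no selection at signing.

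**3. Illustration of selective non-signing.** No input here comes from the documents. True HR is 1.00, weaning times are exponential and losses occur in the CDS arm only. The large-sample Cox HR among retained children is passed through the full design.

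| Assumed pattern | CDS arm lost | Apparent HR | False superiority | Promising or better |
|---|---|---|---|---|
| No selection | 0% | 1.00 | about 0.09 | about 0.16 |
| Unsigned, but unrelated to prognosis | 10% | 1.00 | about 0.09 | about 0.16 |
| Slowest third twice as likely unsigned | 10% | 1.01-1.02 | about 0.12 | up to about 0.21 |
| 30% of children are slow weaners (hazard 0.4-0.5 of the rest), 10% of them unsigned | 3% | 1.01-1.02 | 0.11-0.12 | 0.19-0.20 |
| Same, 30% of them unsigned | 9% | 1.04-1.06 | 0.17-0.21 | 0.26-0.32 |
| All losses from the slowest third (SD of log hazard 0.5-0.7) | 10% | 1.06-1.07 | 0.21-0.24 | 0.31-0.35 |

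In the last row, 10% of the arm drawn from one third of it means that 0.10/(1/3) = 30% of the slowest third goes unsigned.

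**4. Would arm counts reveal it?** With 10% of the CDS arm lost, the expected CDS count among 350 signed is 350 × 0.9/1.9 = 166, against 175 under balance. The SD of that count under 1:1 is √(350 × 0.25) = 9.4. The shortfall is about 1 SD, so enrollment counts alone would not expose it.

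**5. Mechanism.** Digit parity is deterministic. Sequential assignment does not make it random; at most, parity is unrelated to prognosis, which can be checked. The identifier is specific to a hospital encounter, so a second HFNC decision in that encounter must receive the same arm. The effective unit is the encounter, not "the unit of randomization is a clinician-patient decision moment".

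**The case against.** The strongest reply is that a clinician who dislikes the displayed arm need not abandon the plan. The arm can be changed inside it, and the child still counts in the assigned arm. The only stated reason for removing the plan is ineligibility. This stands, and it lowers the incentive for selective non-signing. It does not eliminate it: several eligibility criteria need judgement, and that judgement is made with the arm on screen.

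It is also fair that the larger figures in the table rest on a one-sided, concentrated loss that nothing in the documents supports. Milder patterns give about 12%, and non-signing unrelated to prognosis gives no bias.

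The article plans treatment-assignment summaries and has severity scores available. These help, but would not reliably detect a small loss.

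A reader might infer more than the text supports:

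- *Clinicians can predict the arm before opening the plan.* The key is described as not readily apparent to them, so the exposure is reaction after opening.
- *Consecutive registrations share an arm in runs.* That depends on which digit is used, which is not stated, and no link between parity and prognosis is shown.
- *The diagnosis-code condition biases the comparison.* No reason appears why coding should depend on a weaning prompt.
- *The primary set should become every opened plan.* The criteria are displayed inside the plan, so that set would include children correctly removed as ineligible. The Endpoints section starts the clock at initiation of the plan, so time zero for unsigned children is not defined. The article also does not say that openings are logged.

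**Conclusion.** The concern holds as a weakness in concealment, not as demonstrated bias. The arm is visible before the discretionary signature that defines inclusion, and the intention-to-treat label covers arm changes after signing but not selection at signing. Direction and size cannot be learned from the documents.

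On the stated assumptions (no true effect, 9-10% of the CDS arm unsigned, all slow weaners), false superiority rises from about 9% to 17-24%. With slow weaners only twice as likely to go unsigned, it is about 12%. These results use a normal approximation and count every child as an event.

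Separately, the claim that sequential identifiers ensure random distribution is wrong, and the stated unit of randomization conflicts with a digit fixed per encounter. Both are errors of description; neither is shown to cause bias.

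**What to change.** 1. Keep the current primary analysis set.
2. Pre-specify a sensitivity analysis by digit parity of all encounters under 2 years with HFNC and a qualifying diagnosis code in the study window, signed or not, with time zero at documented HFNC start. The arm can be computed from the identifier for every encounter, so selection at signing cannot affect this comparison.
3. Report signed and total eligible counts by parity, opened counts if they are logged, and baseline severity by parity.
4. State in advance that a superiority or promising conclusion will be qualified if these differ by arm or if the sensitivity analysis disagrees.
5. State the unit of randomization as the encounter, with one record per encounter, and replace the sentence on sequential identifiers with a parity-balance check.

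The cost is some plan wording and one extra query of the existing warehouse. The sensitivity analysis will dilute the effect, because it includes children whose clinician never signed the plan. A somewhat smaller HR there is expected and should not by itself count as disagreement.
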